##### Maternal Fat Mass and Fat-Free Mass

Maternal body composition will be measured through the DTM technique, providing calculated fat mass and fat-free mass [24]. Participants will be asked to collect their own saliva sample 4 hours (or at least between 3 and 4 hours) after administration of the stable isotope, using the same methods used by the researcher at visit 1. They will be provided with equipment and instructions and asked to store the sample in their refrigerator until it is collected by a researcher at the second visit.

#### Human Milk Sample Collection

At the end of the DTM assessment period, a subsample of a complete human milk sample (full expression) will be collected from the participant in their home. At visit 4, participants will either be provided with a sterile breast pump (manual or electric) and collection bottle or given the option of using their personal breast pump, depending on preference. For those using their own pump, a microwave steam sterilizer bag (Medela or New Beginnings) will be provided so that the participant can sterilize the pump parts prior to expression, to minimize contamination.

Participants will be asked to, prior to expression, to clean their hands and the breast area with demineralized water and a cleaning gauze as provided, in order to remove any trace elements from creams that may have been applied to the hands or nipple area (eg, barrier creams, which commonly contain zinc). Participants will be asked to express a full milk sample from 1 breast in the morning (before 12 PM), at least 2 hours after the last feeding or pumping session on that breast, to standardize the collection period.

This method of human milk collection has been shown to be representative of the milk that an infant consumes, and by standardizing the collection period for all participants, the samples will be appropriate for comparisons between participants at the same time point post partum [62]. Participants will be asked to gently invert their full milk sample 3 times immediately after collection and then pour a 12-mL subsample into a collection container provided by the study that has been labeled with the participant ID and to indicate on the container the volume collected. The 12-mL amount was chosen to balance analytical needs (this is the volume required for the planned analyses) with sensitivity to mothers who may have concerns about their milk supply (their infant can be fed the remainder of the expressed milk).

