Visit 2: 2-3 days after baseline	Follow-up (postdose) saliva samples (mother and infant) Collect postdose saliva sample, that was self-collected by the mother after visit 1 (mother only)
Visit 3: 6-7 days after baseline	Follow-up (postdose) saliva samples (mother and infant)
Visit 4: 13-14 days after baseline	Final (postdose) saliva samples (mother and infant) Anthropometry (infant only)
Human milk collection: approximately 3 days after visit 4	Collection of 12 mL subsample of full milk expression from single breast
Visit 5: 2 weeks after visit 4	Anthropometry (infant only) Single test-weigh = weight before and after a breastfeed (infant) Breastfeeding assessment Oral assessment D-MER^a^ questionnaire

^a^D-MER: dysphoric milk ejection reflex.

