The elimination of D_2_O from the mother and transfer to the infant will be traced over the 14-day collection period through analysis of deuterium enrichment of the saliva samples. Postdose (D_2_O) saliva samples will be collected using the same methods described above from the mother and infant at 3 time points: 2 to 3 days postdose, 6 to 7 days postdose, and 13 to 14 days postdose. The reduced sampling protocol from the original International Atomic Energy Agency (IAEA) protocol will be used [24], which has shown high sensitivity and specificity [33].

Infant morbidity will be assessed at visits 3 and 4 with a one-off question: “Has baby been unwell in the last week?” to determine whether any illness occurred over the DTM period.

Any participants expressing breast milk will be asked to weigh and record the amount of milk expressed and indicate whether this was fed back to the infant, either fully or partially, during the 14-day DTM period. An expression log and electronic kitchen scale (Salter, model 1023) will be provided to the participant for recording purposes. Participants will be asked not to feed the infant any expressed milk that had been stored prior to the consumption of D_2_O, as this cannot be tracked; therefore, infants will only consume expressed milk from the 14-day DTM period. Specific expression storage bags will be provided to participants to ensure accurate tracking of milk expressed during the DTM period and to minimize any confusion with milk expressed and stored outside of this time.

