**Infant factors**			
	Age	It is known that infant intake varies over the course of lactation.	Bandara et al [39] da Costa et al [23] Whitehead et al [41] Brown et al [42] Haszard et al [31]
	Body weight	Infants with smaller body weight may have lower intake.	Bandara et al [39] Daniels et al [22] Agne-Djigo et al [43] Haisma 2003 [34] Haszard et al [31]
	Demand vs schedule feeding	Infants fed on demand rather than by schedule may have higher intake.	Dewey et al [44] Haszard et al [31]
	Growth trajectory	Infants with greater growth velocity may have higher intake.	Olga et al [36]
	Household temperature and humidity	Higher household temperature and humidity may be associated with higher intake.	Baby et al [81]
	Number of breast feeds (average per day)	Infants feeding more often may have higher intake.	Brown et al [42] Haszard et al [31]
	Sex	Male infants may have higher intake than female infants.	da Costa et al. 2010 [23]
	Spilling (average quantity)	Hypothesis that intake may differ in infants who spill.	N/A
	Term, preterm, or early term	Infants born early may have lower intake.	Lapillonne et al [82] Altuntas et al [83] Boies and Vaucher [84]

^a^D-MER: dysphoric milk ejection reflex.

^b^N/A: not applicable.

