#### Data Analysis Plan

Human milk intakes of infants aged 3 months will be described. Perception of milk supply will be collected as a continuous scale and dichotomized to create a variable for comparing low (insufficient) perceived milk supply and high (oversupply) perceived milk supply. Regression models will be used to assess how maternal perception of human milk supply (categorical independent variable) is associated with actual human milk volumes produced by lactating participants at 3 months post partum (dependent variable). Mean differences and 95% CIs will be estimated. Similarly, the relationships between predetermined potential predictors (Table 1) of human milk intakes and actual milk intakes will be described using regression modeling. Residuals of regression models will be plotted to assess homoscedasticity and normality. Results will be presented for descriptive purposes; therefore, no adjustment for confounders will be made. However, moderation by demographic characteristics will be investigated descriptively by presenting stratified results. Data will be illustrated graphically where appropriate.

To understand whether certain factors predict breastfeeding problems, the breastfeeding assessment tool will be used. These data will be analyzed using prediction modeling techniques, including a combination of linear regression models (reporting *R*^2^), and least absolute shrinkage and selection operator regression, to understand which factors might combine to predict breastfeeding problems. In addition, if there are any modifiable factors indicated to cause breastfeeding problems, a causal inference approach to analysis will be used to determine which confounders to include in the model, including the development of a directed acyclic graph.

BMI and weight velocity between birth and age up to 5 months will be calculated from the Well Child Tamariki Ora data collected. An initial investigation will be conducted into whether infant milk intakes and infant growth over time (birth to age up to 5 months) can be used to assess human milk inadequacy (actual low milk volume) using regression models.

Statistical analyses will be conducted under the guidance of a biostatistician using Stata (version 18; StataCorp LLC) software.

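### The milk-sampling rule sets a minimum interval, not a standardized one, so the interval could confound the composition-volume association

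*Protocol article*

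**What the plan says.** Under Human Milk Sample Collection, the mother expresses fully from one breast, before noon, "at least 2 hours after the last feeding or pumping session on that breast, to standardize the collection period". The next paragraph draws the conclusion: "by standardizing the collection period for all participants, the samples will be appropriate for comparisons between participants" at the same time post partum. The container carries the participant ID, and the mother is asked "to indicate on the container the volume collected". No other item to be recorded at sampling is named.

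The expression log is described under Human Milk Volume. It covers milk expressed and whether it was fed back, "either fully or partially, during the 14-day DTM period". The milk sample comes after that period, according to Table 1: "Human milk collection: approximately 3 days after visit 4".

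On feeding frequency, Table 2 says: "Infants feeding more often may have higher intake". The average number of feeds in 24 hours is asked in the main questionnaire at visit 1 (Health History). Secondary objective 4 is the association between composition and volume. The Data Analysis Plan says results are descriptive and "therefore, no adjustment for confounders will be made".

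**The concern.** A lower bound does not standardize an interval. One mother may express 2 hours after a feed and another after a whole night without feeding from that breast, and both follow the instructions. The other parts of the rule (full expression, one breast, morning) fix other conditions, and the morning limit still admits overnight gaps.

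This would be mere noise if the interval were unrelated to volume. The article gives a reason to think otherwise: it expects more frequent feeding to go with higher intake, and mothers who feed more often will tend to have shorter gaps. If the interval also affects the concentration of a nutrient, part of any association between composition and volume would reflect when the sample was taken. The same could happen in the comparison of composition by perceived supply. All nutrients come from the same expression, so they share the same interval. The Discussion says that a link between perceived insufficient supply and nutrient concentrations could be a biological basis for individualized interventions, so the source of any association matters.

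**Working it through.** **1. The plan's own figure.** The Sample Size section gives a 95% half-width of 0.18 SD with 120 complete dyads. 1.96/√120 = 0.179, so it reproduces. So do the recruitment target, 120/0.80 = 150, and the implied SD, 27/0.18 = 150 mL/day. None of this is in dispute. It supplies n = 120 for what follows.

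**2. How the article handles timing elsewhere.** Where timing matters for the isotope method, the windows have two sides: maternal saliva at 3 to 4 hours, and postdose samples at 2 to 3, 6 to 7 and 13 to 14 days. The milk sample has a lower limit only.

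**3. What could supply the interval.**
- The container label: volume and ID are named, times are not.
- The expression log: it covers the 14-day period and records amounts. The sample falls about 3 days after visit 4, that is about 16 to 17 days after baseline.
- Average feeds per 24 hours: collected at visit 1, so over two weeks before the sample. It describes habit, not the gap on that breast that morning, and is a partial proxy only.

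**4. Illustration of size.** The documents give no correlation of the interval with volume or with any nutrient, so every input here is an assumption. With no true association,

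induced r = r(interval, volume) × r(interval, nutrient).

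The probability of a nominally significant result at two-sided 5% and n = 120 follows from Fisher's z, with λ = atanh(r) × √117:

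P = Φ(λ − 1.96) + Φ(−λ − 1.96).

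| Assumed correlations (absolute values) | Induced r | Probability of p < 0.05 |
|---|---|---|
| 0.2 × 0.2 | 0.04 | 7% |
| 0.3 × 0.3 | 0.09 | 16% |
| 0.3 × 0.5 | 0.15 | 37% |
| 0.4 × 0.4 | 0.16 | 42% |
| 0.5 × 0.5 | 0.25 | 79% |

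For 0.3 × 0.3: λ = 0.0902 × 10.82 = 0.98, and P = Φ(−0.98) + Φ(−2.94) = 0.16. The 95% limit for r under no association is tanh(1.96/√117) = 0.18. The sign of the induced correlation depends on how the interval acts on each nutrient, which is not given. If the interval has no effect on a nutrient, the induced correlation for that nutrient is zero.

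**5. How many samples a change could reach.** By January 17, 2026, 91 of 150 dyads were enrolled, leaving 150 − 91 = 59, or about 59 × 0.80 = 47 with complete data. Some of the 91 may not yet have given milk at that date. Against that, enrolment continues until any change is made. At n = 47 the half-width for a correlation near zero is 1.96/√44 = 0.30 on Fisher's z scale.

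**The case against.** A reader might infer that the interval is not recorded and so can never be adjusted for. The article does not support that. It names the volume on the container and is silent on anything else. Milk is collected from the participant on the day of expression, and the fields of a sample form are detail that an article commonly leaves to the full protocol. Part of the path, through habitual feeding frequency, could also be addressed with the feeds per 24 hours already collected.

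A reader might also infer that the interval is shown to vary with volume. It is not. Table 2 says only that frequent feeders may have higher intake, on a daily average. The gap here is one gap, on one breast, on one morning. The link is plausible and no more.

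Three further objections carry weight. The collection method rests on a cited source that cannot be seen here, so a 2-hour floor may be adequate for some nutrients. The correlations used for size are assumed, and the induced values of 0.09 to 0.15 lie inside the 0.18 limit. And the absence of adjustment is a declared choice for a descriptive study that claims association only.

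The first two limit how strongly the point can be put, but they do not remove it. A bias inside the limit still raises the chance of a spurious finding, and more participants do not reduce it. On the third, the interval is partly a condition of how the sample was taken, so an association created by it would not describe the milk, even in a descriptive analysis.

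**Conclusion.** The point holds in a limited form. The article calls the collection period standardized and bases comparability on it, but the interval has only a lower limit. The article does not state whether the actual interval is recorded, and no confounder adjustment is planned. The interval could therefore confound secondary objective 4 and the comparison of composition by perceived supply.

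This rests on two assumptions that the documents make plausible but do not establish: that the gap before sampling follows habitual feeding frequency, and that it affects concentration. Setting a minimum interval suggests that the authors think the gap matters, but no effect is given. The size is unknown, and the table above is an illustration only. The no-adjustment sentence follows the perception and predictor models, and the Data Analysis Plan describes no separate composition model. I read the sentence as general.

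The primary objective, mean milk intake by the isotope method, is unaffected. This is a worthwhile improvement to a secondary analysis, not a flaw that threatens the study.

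**What to change.** 1. Unless the times are already captured, have the mother write two clock times beside the volume: the last feed or pump on that breast, and the start of expression.
2. Keep the unadjusted composition results as planned. Add a sensitivity analysis that adjusts for the interval, and refit the unadjusted model in the same participants, so that a change of model is not mixed with a change of sample.
3. For participants without the times, use average feeds per 24 hours as a partial proxy and label it as such. It is itself a listed predictor of intake, so adjusting for it may also remove part of a real association.
4. Describe the rule as a minimum interval rather than a standardized collection period.

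The cost is two entries on an existing label and one additional model. The downside is that the interval will be missing for samples already collected. With about 47 complete new samples at most from dyads not enrolled by January 17, 2026, the adjusted estimate will be imprecise (half-width about 0.30, against 0.18 in the full 120). If the times are already on a form, only steps 2 and 4 are needed, and the adjusted analysis can use every sample with recorded times.

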#### Breastfeeding Observation

A one-off breastfeeding will be observed in the final visit (visit 5) by an IBCLC. The IBCLC will use the Bristol Breastfeeding Assessment Tool [63] to assess adequate latch and transfer of milk by the infant. This tool has 4 main elements, scoring a breastfeeding on positioning, sucking, swallowing, and attachment. A score of 0 (poor feeding elements) to 8 (good feeding elements) will be recorded by the IBCLC on the standardized Bristol Breastfeeding Assessment Tool form [63].

#### Test Weighing

During the breastfeeding observation by the IBCLC, a single test weighing of human milk transfer will be taken using an electronic baby scale (Seca model 334 or Marsden model M-300). Single test weighing, the process of weighing the infant before and after a single breastfeed, is often used clinically by health care professionals working with breastfeeding dyads to assess adequate milk transfer. The volume of milk transferred in the single test weighing will be compared with the human milk volume estimated by the DTM technique to investigate whether a one-off test weighing is indicative of actual human milk volume over a 2-week period.

#### Anthropometry

Infant weight and length will be measured using an electronic baby scale (Seca model 334) and a 99-cm measuring mat (Seca model SE210). Infants will be weighed naked with only a dry nappy of known weight. Maternal weight (minimal clothing, no shoes) will be measured using an electronic scale (Tanita model HD-351), and height will be measured using a portable stadiometer (Wedderburn model WMHM200P or Seca model 213), depending on whether the visit is at the participants’ home or in the clinic. Measurements will be conducted by trained research staff in duplicate, following the World Health Organization (WHO) anthropometric protocol [64]. A third measurement will be taken if the difference between the first and second measurements exceeds the maximum allowable difference (0.1 kg and 0.5 kg for infant and maternal weight, respectively, and 0.7 cm for length and height).

At visit 5 (the final visit), photographs will be taken of anthropometric measurements collected during Well Child Tamariki Ora visits. These will be entered into REDCap. Well Child Tamariki Ora visits are free health assessments that are offered to all New Zealand families and conducted between ages 6 weeks and 5 years [65]. These anthropometric data will be used alongside those directly measured in the study to assess infant growth trajectory over time, which will be compared with the WHO Child Growth Standards [66]. Infant weight and length data will be used to calculate BMI and determine BMI-for-age *z* score using sex-specific reference data from the WHO Child Growth Standards [66].

#### Perception of Infant and Maternal Sleep

Infant sleep will be assessed using questions from a New Zealand sleep study [67], modified to include questions about infant sleep location and changes to infant sleep patterns. Participants will be asked a question about their own sleep quality and sleep quantity, developed by the research team, in the main questionnaire to assess maternal sleep perception.

#### Potential Predictors of Human Milk Intake

##### Overview

Human milk intake is complex and can be influenced by a range of different factors. A selection of potential maternal and infant factors that may influence human milk intakes has been identified through literature searches and advice from breastfeeding experts. These are summarized in Table 2.

**Table 2 table2:** Potential predictors (maternal and infant) of human milk intakes.

Factors that potentially predict human milk intakes		Explanation of potential impact or hypothesis	References
**Maternal factors**			
	Breastfeeding self-efficacy	Mothers who have greater self-efficacy may have infants with higher intake.	Khresheh and Ahmad [68]
	Breast or chest trauma	Mothers who have experienced breast or chest trauma may have infants with lower intake.	Kraut et al [69] Haifeng et al [70] Stopenski et al [71] Leal et al [72] Holmgren et al [73]
	Cannabis	Mothers who use cannabis may have infants with lower intake.	Castro-Navarro et al [46]
	D-MER^a^	Mothers who experience D-MER (sudden, intense negative emotions that occur immediately before and during milk let-down) may have infants with lower intake.	Ureño et al [74]
	Early return of menses	Mothers who have had return of menses may have infants with lower intake.	Spencer et al [49]
	Education	Mothers who are more educated may have infants with higher intake.	Bandara et al [39] Haszard et al [31]
	Employment (current)	Mothers who are in current employment may have infants with lower intake.	Haszard et al [31]
	Following specific diet	Mothers who are consuming specific dietary patterns (eg, low fat, dairy-free, and vegetarian) may have infants with differing intake.	Spencer et al [49]
	Galactagogues or antigalactagogues	Mothers who are consuming galactagogues (a substance that is thought to increase milk volume) may have infants with higher intake, and mothers who are consuming antigalactagogues may have infants with lower intake.	Brodribb et al [75] Johnson et al [76]
	Hormonal birth control	Mothers who are taking hormonal birth control may have infants with lower intake.	Berens et al [77]
	Maternal BMI	Mothers with higher BMI may have infants with lower intake.	Hilson et al [40] Haszard et al [31]
	Maternal fat mass	Mothers who have higher fat mass may have infants with lower intake.	Diana et al [78]
	Parity	Mothers who have previously given birth may have infants with lower intake.	Whitehead et al [41]
	Previous breastfeeding experience	Mothers with previous breastfeeding success may have infants with higher intake, while those who did not have success previously may have infants with lower intake.	Huang et al [79]
	Maternal morbidities	Mothers who have medical conditions may have infants with lower intake.	Spencer et al [49]
	Maternal sleep	Hypothesis that maternal sleep may impact infant milk intake.	N/A^b^
	Maternal use of medications	Mothers on certain medications may have infants with differing intake.	Farah et al [48]
	Mental health	Mothers who experience challenges with mental health may have infants with lower intake.	Spencer et al [49]
	Pain while breastfeeding	Mothers who experience pain while breastfeeding may have infants with lower intake.	McGuire [80]
	Smoking or nicotine	Mothers who use nicotine may have infants with lower intake.	Napierala et al [47]
	Stress	Mothers with higher levels of stress may have infants with lower intake.	Nagel et al [50]
**Infant factors**			
	Age	It is known that infant intake varies over the course of lactation.	Bandara et al [39] da Costa et al [23] Whitehead et al [41] Brown et al [42] Haszard et al [31]
	Body weight	Infants with smaller body weight may have lower intake.	Bandara et al [39] Daniels et al [22] Agne-Djigo et al [43] Haisma 2003 [34] Haszard et al [31]
	Demand vs schedule feeding	Infants fed on demand rather than by schedule may have higher intake.	Dewey et al [44] Haszard et al [31]
	Growth trajectory	Infants with greater growth velocity may have higher intake.	Olga et al [36]
	Household temperature and humidity	Higher household temperature and humidity may be associated with higher intake.	Baby et al [81]
	Number of breast feeds (average per day)	Infants feeding more often may have higher intake.	Brown et al [42] Haszard et al [31]
	Sex	Male infants may have higher intake than female infants.	da Costa et al. 2010 [23]
	Spilling (average quantity)	Hypothesis that intake may differ in infants who spill.	N/A
	Term, preterm, or early term	Infants born early may have lower intake.	Lapillonne et al [82] Altuntas et al [83] Boies and Vaucher [84]

^a^D-MER: dysphoric milk ejection reflex.

^b^N/A: not applicable.

